
### Dissemination policy

This trial is intended for publication in international peer-reviewed journals. The results of this study will also be presented at internationally relevant scientific meetings. The progress and the results of the study will be saved at Clinicaltrials.gov to allow general access to documented findings.

## Discussion

Despite the increasing incidence of proximal gastric cancer and P/GEJ cancers [20], the optimal treatment strategy for those cancers, including regimens of adjuvant and neoadjuvant therapy and extent of gastrectomy (such as when a transthoracic approach or TG is needed), remains unknown.

The optimal operation for P/GEJ cancers should achieve complete removal of the primary cancer and regional LNs that harbor risks of metastases while maintaining the best possible QoL for the patient. It should also facilitate a quick return to intended oncologic therapy such as adjuvant chemotherapy. In this context, it is unknown whether and the extent to which PG would result in better QoL than TG.

Kunisaki et al. conducted a PGSAS NEXT survey study of gastric cancer patients who underwent TG or PG [21]. This study utilized a questionnaire developed for postgastrectomy patients in Japan (PGSAS-45), which was validated in patients with stage I gastric cancer without receipt of adjuvant or neoadjuvant therapy [22]. PGSAS-45 consists of 45 question items, and 19 subscale “main outcome measures” are calculated on the basis of responses. The PGSAS NEXT study enrolled 1,020 TG patients and 518 PG patients. The PG patients had better scores in several main outcome measures (weight loss, dumping syndrome, necessity for additional meals, ability to work, dissatisfaction with working, and dissatisfaction with daily life subscales; all *p* < 0.05) and a trend towards a better score in the reflux subscale. This study included a large number of patients, and the results supported the use of PG. However, the following limitations made interpretation of the study results difficult: unbalanced disease stage (more advanced tumors underwent TG and extended LN dissection) and surgical approach (more patients in TG underwent open approach) between groups, reconstruction methods after PG not standardized, and cross-sectional study design, which meant that the survey was sent at various times after surgery.

The KLASS-05 randomized controlled study (NCT02892643) [23] recently reported results at the International Gastric Cancer Congress 2022. At 2 years after surgery, hemoglobin level changes did not differ between the laparoscopic TG and PG groups (*P* = 0.349), but a lower proportion of patients required vitamin B_12_ supplementation in the PG group (14.7% vs. 58.0%, *p* < 0.001). Moreover, late complications occurred more frequently among the TG group than the PG group (14.3% vs 10.8%, *p* = 0.738), and there was no increased incidence of reflux esophagitis after PG. The PG group had better physical functioning (*P* = 0.025) and social functioning (*P* = 0.031) at 2 years after surgery, suggesting an overall better QoL after PG, although the difference was not robust. QoL measurements were secondary outcomes in the KLASS-05 study and were only collected at the 2-year postoperative time point; therefore, the short-term QoL benefits of laparoscopic PG remain unknown.

The main focus of our proposed study will be the short-term QoL benefits of MIPG versus MITG, with the primary outcome being appetite level score at 3 months. We will utilize MDASI-GI [19], which is concise and written in easy-to-understand language, asking patients to score severity of symptoms experienced in the past 24 h, although it may not adequately identify less frequent symptoms that would be affecting patients’ quality of life. Although we added three fit-for-purpose question items to MDASI-GI for a total of 27 question items (MDASI-GI +), with its relatively small number of question items as compared to other validated questionnaires (e.g. EORTC QLQ-C30 plus STO22, with a total of 52 question items), MDASI-GI + may not detect details of postgastrectomy symptoms. However, after careful consideration of a choice of questionnaire to be used in this study, MDASI-GI + with its simple structure, which is expected to take less than 3 min for patients to complete, was considered an ideal questionnaire to be used in multiple languages and can be conveniently repeated to enable our longitudinal survey study.

This proposal is novel because it is the first international collaborative study as well as the first American study to prospectively investigate the benefits of MIPG with anti-reflux techniques. The research is culturally innovative because we will focus on PRO as the primary outcome, thus promoting a growing appreciation of the importance of patient-oriented care in the field of surgical oncology [24]. Theoretical benefits of PG, such as an improved hemoglobin level and reduced weight loss, become clinically significant only when QoL is improved, which can only be measured using PROs. The primary endpoint (appetite level) will be serologically validated with ghrelin level, which is an appetite-stimulating hormone that is known to decrease after TG [5]. Expected confounding factors that would affect postgastrectomy PROs, such as use of neoadjuvant therapy and different types of reconstruction after PG, will be carefully analyzed in sensitivity analyses. In addition, our study will determine the safety and feasibility of MIPG (including using a robotic approach) in the international setting. This transpacific collaboration between high-volume academic cancer centers will establish the foundation for future larger trials in the field of gastric cancer surgery.

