## Background

The current standard surgical procedure used to treat proximal gastric and gastroesophageal junction (P/GEJ) cancers with limited esophageal extension is total gastrectomy (TG), unless the tumor is small (< 3 cm in diameter) and contained in the mucosal layer (pT1a); such tumors can be removed via endoscopic mucosal resection [1]. TG is associated with impaired appetite and weight loss [2–4] due to the loss of gastric functions such as production of ghrelin (the “hunger hormone” secreted by the stomach) [5] and with anemia due to intrinsic factor loss and vitamin B_12_ malabsorption. Theoretically, proximal gastrectomy (PG) can mitigate these problems by preserving gastric function. However, PG with direct esophagogastric reconstruction is associated with severe postoperative reflux and poor quality of life (QoL) and is therefore rarely performed in Western countries, including the United States [6, 7]. The lack of an effective surgical procedure that preserves gastric function and postoperative QoL for patients with P/GEJ cancers is a critical gap.

With the recent development of effective post-PG anti-reflux reconstruction techniques, such as double-tract reconstruction and the double-flap technique, PG has been increasingly used to treat proximal gastric cancer in South Korea and Japan [8–13]. Researchers in the KLASS-05 trial (NCT02892643) have recently reported results comparing outcomes at 2 years after PG with outcomes at 2 years after TG in patients with cT1N0 proximal gastric cancer, and these results showed that PG reduced the need for vitamin B_12_ supplementation and improved some QoL measurements. However, it remains unknown whether PG with double-tract reconstruction or the double-flap technique has short-term postoperative QoL advantages over TG [8, 12, 13]. In addition, the theoretical disadvantages of PG include incomplete lymph node (LN) removal, which may result in recurrence, and the potential for a second gastric cancer in the remnant stomach. Moreover, delayed gastric emptying of the remnant stomach can cause upper gastrointestinal symptoms such as reflux and bloating. The QoL benefits of PG must therefore be clearly demonstrated before encouraging its use in Western countries.

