### Rationale

Surgeons at The University of Texas MD Anderson Cancer Center in Houston, Texas; the Mayo Clinic in Rochester, Minnesota; Memorial Sloan Kettering Cancer Center, New York; Yonsei University in Seoul, South Korea; and Keio University in Tokyo, Japan formed a collaboration to address the issue of the surgical approach for P/GEJ cancers, an internationally important but controversial topic that requires immediate action. Our central hypotheses are that PG is safe and that patients have improved levels of appetite after minimally invasive PG (MIPG) with effective anti-reflux techniques because of maintained secretion of ghrelin from the gastric remnant, which leads to better overall QoL compared with minimally invasive TG (MITG). The rationale for this project is that MIPG’s theoretical benefit of preserving gastric function, which can only be measured using patient-reported outcomes (PROs), must be demonstrated before widespread implementation of MIPG.

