### Study objectives

The primary objective is to compare the short-term appetite of patients who undergo MIPG for gastric and gastroesophageal adenocarcinoma with that of patients who undergo MITG. We hypothesize that MIPG is associated with higher postoperative appetite levels compared with MITG, which would result in better nutritional status and less body weight loss after surgery.

The secondary objective is to assess PROs and nutrition measures and compare them between the MIPG and MITG groups. We will use the MD Anderson Symptom Inventory Gastrointestinal Cancer Module (MDASI-GI) questionnaire, along with an additional three experimental question items (MDASI-GI +), to collect preoperative and postoperative PRO measures of QoL, and we will check fasting ghrelin levels to correlate them with reported appetite levels. We will also investigate factors associated with improved QoL after surgery, safety of MIPG and MITG, and oncologic outcomes after MIPG and MITG.

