### Statistical methods

The primary outcome is appetite level score (with 0 being the best and 10 being the worst) according to the MDASI-GI + (Question #8) at 3 months after surgery. We will enroll a total of 64 patients in order to have 60 evaluable patients at 3 months after surgery (i.e., assuming a 5% attrition rate). With 30 patients expected in each cohort, this study will have 80% power to detect a one-point difference in appetite level score using a two-sample *t*-test with a 5% significance level and assuming a common standard deviation of 1.35 (nQuery Advisor 7.0). We will also compare serum ghrelin levels at 3 months after surgery. For the primary analyses, we will apply the inverse probability treatment weights using propensity scores for assessing the difference between the two surgical groups. Inverse probability weighting is applied by weighting the outcome measures by the inverse of the probability of an individual with a given set of covariates being assigned to their treatment (i.e., propensity score). The propensity scores will be derived through fitting a multiple logistic regression model with MIPG (vs. MITG) as the outcome variable. Then, in the presence of measured confounders, we can estimate the difference between the two treatment groups via inverse probability weighting of the study subjects. For the regression analyses described below for assessing the “surgical procedure” effect, the inverse probability treatment weights using propensity scores will be applied as appropriate in addition to any standard statistical methods. The two-sample t-test or Wilcoxon rank-sum test will also be used to compare the appetite level or ghrelin level at 3 months, as well as the percent change from baseline, between the two cohorts. We will longitudinally collect PROs (using the fully translated MDASI-GI +) and compare specific items and overall scores as well as body weight, body mass index, and albumin and hemoglobin levels at 1, 3, 6, and 12 months after surgery in the cohorts. A linear mixed effects model will be fit to assess the change in QoL over time while accounting for potential intra-patient correlations. “Time” points will be included as a fixed effect, and “patient” will be included as a random effect. The surgical procedure received and use of adjuvant or neoadjuvant therapy will be included as covariates. Similar analyses will be performed to assess the changes in body weight, body mass index, and albumin and hemoglobin levels over time. The number of LNs examined pathologically, incidence of postoperative complications, operating room time, blood loss, and length of hospital stay will be compared. Continuous variables (such as length of hospital stay) will be assessed using the two-sample t-test or Wilcoxon rank-sum test. Categorical variables (such as type and severity of complications) will be assessed using Fisher’s exact test. Local–regional recurrence-free and overall survival will be estimated using the Kaplan–Meier method, and Cox regression analyses will be performed to assess the association with patient characteristics and surgical procedure received. The 3-year loco-regional recurrence rate will be estimated along with the 95% confidence interval. Missing data will be excluded from analysis and no missing data imputation will be performed. Sensitivity analyses to investigate factors associated with PRO scores, including but not limited to country (west vs. east), tumor location, types of reconstruction after PG, use of neoadjuvant and adjuvant therapy, use of jejunostomy or nutrition status, on PRO scores will be performed.

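### Correlating ghrelin with appetite cannot validate the appetite endpoint unless the analysis accounts for procedure, and the protocol article does not say that it will

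*Protocol article*

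**What the plan says.** Four parts of the protocol article bear on this.

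- **Discussion.** The primary endpoint "will be serologically validated with ghrelin level", and the same sentence describes ghrelin as a hormone "which is an appetite-stimulating hormone that is known to decrease after TG".
- **Background.** Impaired appetite and weight loss after TG are put down to lost gastric function: "due to the loss of gastric functions such as production of ghrelin".
- **Study objectives and Rationale.** Under the secondary objective, "we will check fasting ghrelin levels to correlate them with reported appetite levels". The Rationale attributes the expected appetite benefit of minimally invasive proximal gastrectomy (MIPG) over minimally invasive total gastrectomy (MITG) to ghrelin: "because of maintained secretion of ghrelin from the gastric remnant".
- **Statistical methods.** "We will also compare serum ghrelin levels at 3 months after surgery". A t-test or rank-sum test "will also be used to compare the appetite level or ghrelin level at 3 months". These compare each variable between the groups. The section describes no analysis that links the two variables.

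No section says that the correlation will be pooled over procedures, and none says that it will be stratified by or adjusted for procedure.

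**The concern.** By the article's own account, the procedure determines ghrelin through anatomy. By its hypothesis, the procedure also determines appetite. Procedure is then a common cause of both variables, and two variables that share a cause can be correlated across the whole cohort even if, among patients who had the same operation, one says nothing about the other.

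The article names routes other than ghrelin by which appetite could differ between the groups: reflux and delayed emptying of the remnant (Background), choice of procedure by patient and surgeon (Details of surgery), and tumor location, neoadjuvant or adjuvant therapy and jejunostomy (Statistical methods).

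The planned group comparisons do not close the gap. A difference in ghrelin is expected whatever happens to appetite, so finding both differences does not link them. The propensity weighting addresses confounding of the procedure comparison and leaves procedure as a common cause. The mixed model that includes procedure is described for QoL, body weight, body mass index, albumin and hemoglobin, but not for ghrelin.

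At stake is the standing of a single 0–10 item. A claim of serological validation would lend it biological authority, and would appear to support the ghrelin mechanism, on evidence that may reflect only which operation was done.

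**Working it through.** **Inputs from Statistical methods.** 30 evaluable patients per group, a one-point appetite difference, a common SD of 1.35, a 5% level (taken as two-sided), 5% attrition, and a score on which 0 is best and 10 is worst.

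**Assumptions.** The article gives no ghrelin mean, SD or expected difference. The standardised ghrelin difference between procedures, dG, is therefore varied from 0.5 to 3 SD. The true correlation within each procedure is set to zero, so every significant result is false.

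**Step 1: reproduce the plan's own figure.** The standard error is 1.35 × √(2/30) = 0.349, and 1/0.349 = 2.87. The normal approximation gives power Φ(2.87 − 1.96) = 81.8%; the t-test gives 80.5%. The stated 80% reproduces. Attrition: 60/0.95 = 63.2, rounded up to the stated 64.

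**Step 2: expected correlation when procedure is ignored.** The standardised appetite difference is dA = 1/1.35 = 0.74. With equal groups and no within-procedure link, the size of the correlation is

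r = (dA × dG / 4) / √[(1 + dA²/4)(1 + dG²/4)],

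with a negative sign, because a high score means poor appetite. Here dA²/4 = 0.137.

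- dG = 1: 0.185 / √(1.137 × 1.25) = 0.16
- dG = 2: 0.370 / √(1.137 × 2) = 0.25
- dG = 3: 0.556 / √(1.137 × 3.25) = 0.29

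**Step 3: how often this is significant.** Simulation of 20,000 studies per setting, 30 patients per group, two-sided 5% Pearson test. Entries are the share of studies with a significant result.

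| Ghrelin difference (SD) | Expected r, one-point appetite difference | Unadjusted, one point | Unadjusted, half a point | Unadjusted, no appetite difference | Adjusted for procedure, one point |
|---|---|---|---|---|---|
| 0.5 | −0.08 | 9.9% | 6.6% | 4.9% | 5.0% |
| 1 | −0.16 | 22.9% | 9.1% | 4.9% | 5.1% |
| 1.5 | −0.21 | 36.5% | 13.5% | 5.1% | 5.0% |
| 2 | −0.25 | 49.2% | 16.8% | 4.6% | 5.1% |
| 3 | −0.29 | 63.5% | 21.9% | 4.9% | 5.0% |

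The artefact needs both differences. With no appetite difference, the unadjusted test stays near 5% for every ghrelin difference. Adjustment for procedure removes the artefact throughout.

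**Step 4: what the adjusted analysis can detect.** By Fisher's z, 30 patients within one procedure give power of about 36%, 60% and 81% for a true r of 0.3, 0.4 and 0.5. All 60 patients give about 65%, 89% and 99%, before a small loss for covariates. One procedure-adjusted analysis of everyone is therefore better than two separate correlations.

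**The case against.** The strongest reply is that the criticised analysis is not in the document. A reader might infer that the protocol plans a pooled correlation. The Study objectives suggest this when read plainly, but they do not say it, and the model for a supportive correlation is ordinary content for an analysis plan that is not shown. This stands as far as it goes: the absence of a model is not the finding. It does not cover the Discussion, which states in advance that the endpoint will be validated.

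A second reply is that low ghrelin after TG does not by itself create a false correlation. That is correct. Appetite must also differ between procedures, at least partly for reasons other than ghrelin. The one-point rows take the whole planned difference as unrelated to ghrelin, which is the unfavourable end for that difference.

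Third, ghrelin and the questionnaire are also collected before surgery, and a baseline correlation cannot be produced by the operation. This is true and useful, but the article does not tie the validation claim to baseline data, and a preoperative association would not by itself establish what the 3-month score measures.

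Fourth, if ghrelin mediates the benefit, adjusting for procedure discards the between-procedure signal. That signal cannot separate ghrelin from anything else that differs between the operations. The step from ghrelin to appetite must itself be estimated conditional on procedure. What remains of this objection is the loss of precision.

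Finally, the article sets neither a significance test nor a threshold for validation, and every rate above depends on an assumed ghrelin difference. Both points are right, so the rates illustrate the risk and do not predict it.

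**Conclusion.** The concern holds in a limited form. Neither a correlation that ignores procedure nor separate group comparisons of appetite and ghrelin can support the claim of serological validation. If the planned one-point difference arises for non-ghrelin reasons and there is no link within procedure, the unadjusted correlation would be significant in about 23% to 64% of studies for assumed ghrelin differences of 1 to 3 SD, against a nominal 5%. At half a point, the range is about 9% to 22%.

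The documents do not support the stronger conclusion that a pooled analysis has been specified, or that a false correlation is bound to appear. The primary endpoint comparison, its weighting and its sample size are untouched. This is an overclaim attached to a supportive analysis, and it is worth correcting before results are known.

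**What to change.** 1. State that the appetite–ghrelin association will be estimated in all evaluable patients by regressing the 3-month Q8 score on 3-month fasting ghrelin, with procedure, baseline Q8 score and baseline ghrelin as covariates. Report the coefficient with its confidence interval.
2. State that an unadjusted correlation, or a group difference in both variables, will not be read as validating the endpoint or confirming the mechanism.
3. In the Discussion, replace the claim of serological validation with wording such as: *explored for association with ghrelin, adjusted for procedure*.

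The change uses data that the trial already plans to collect and needs no extra patients. The cost is a less precise estimate with limited power for modest associations (about 65% for a true r of 0.3 in 60 patients, before the covariates are counted). A null adjusted result should therefore not be presented as refuting the ghrelin mechanism.

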## Data Availability

Not applicable.

## Abbreviations

P/GEJ: Proximal gastric and gastroesophageal junction
TG: Total gastrectomy
PG: Proximal gastrectomy
QoL: Quality of life
LN: Lymph node
MIPG: Minimally invasive PG
MITG: Minimally invasive TG
PRO: Patient-reported outcome
MDASI-GI: MD Anderson Symptom Inventory Gastrointestinal Cancer Module
